### Assignment of interventions: allocation

#### Sequence generation

Eligible patients will be approached for enrollment either in the preoperative clinic or after hospital admission. Surgery will take place within 14 days of enrollment. Randomization will be done within 3 days prior to the scheduled surgery and will occur in a 1:1 ratio.

#### Concealment mechanism

Randomization will occur up to 3 days prior to surgery to avoid selection bias. Allocation will be concealed from all patients. For sites where randomization is completed by the surgeon, allocation will be concealed as much as possible from the research team. This will be further supported using a template for surgical documentation, ensuring adequate documentation without any reference to treatment allocation (Additional file 5). For sites where randomization is completed by the research team, it will not be possible to conceal allocation from the research team. We will use the ITT principle in analyzing the outcomes and make every effort to obtain secondary outcomes. For all eligible non-enrolled patients, the reason for non-participation by either physicians or patients will be documented to develop strategies to minimize their occurrence in the larger trial. Any systematic differences between baseline characteristics of eligible enrolled and not-enrolled patients will be documented.

### Assignment of interventions: blinding

#### Who will be blinded

Trial participants will be blinded to their intervention assignment. Surgeons cannot be blinded as they are performing the allocated intervention, but allocation will be concealed as much as possible from the research team using templates for documentation without reference to treatment allocation.

#### Procedure for unblinding if needed

Blinding of treatment allocation may only be broken with the permission of the principal investigator if the safety of the participant is at risk and providing a treatment plan requires knowledge of study allocation.

### Data collection and management

#### Plans for assessment, collection of outcomes, and data management

The study case report form (CRF) is the primary data collection instrument for the study. Study personnel, including data entry team members, will use source documents to complete case report forms (CRFs). The information outlined in the schedule of events will be documented in the CRFs.

#### Plans to promote participant retention and complete follow-up

To ensure that the trial can successfully recruit the target sample size, only committed high-volume academic centers have been recruited to participate. The rate of retention in this study will be used to optimize compliance in future larger trials. The outcomes likely most vulnerable to loss to follow-up are anticipated to be the mRS and EQ-5D, which require follow-up at 6 and 12 months. Both of these can be obtained using phone communication, which has similar reliability to in-person assessments. For the assessment of preliminary efficacy (progression-free and overall survival), we will establish contact with the patient or the substitute decision-maker (SDM) on at least 3 occasions, especially if the scheduled MRI appointment is missed. Efforts will be made to facilitate alternative MRI dates or provide locations closer to the patient’s address. If the patient’s status is unknown, study sites will issue certified registered letters to their address and search for the death of a patient in local/regional/national death registries or other public collections of such data as permitted by local privacy laws.

#### Confidentiality

Information about study participants will be kept confidential and managed according to the requirements of the Personal Health Information Protection Act of 2004 (PHIPA) and the Research Ethics Board.

#### Plans for collection, laboratory evaluation, and storage of biological specimens for genetic or molecular analysis in this trial/future use

Plans for collection, laboratory evaluation, and storage of biological specimens for genetic or molecular analysis will be in accordance with standard clinical procedures at each academic hospital site.

## Statistical methods

### Statistical methods for primary and secondary outcomes

#### Primary outcome

Descriptive statistics will be used to report the rate of randomization (patients per month) as overall and per site numbers using medians and interquartile ranges (IQR).

#### Secondary outcomes

Descriptive statistics (with corresponding standard deviations (SD) or IQR) will be used for continuous variables while frequencies and proportions (and 95%CIs) will be used to report categorical variables. A priori subgroup descriptive comparisons will include our randomization strata, along with the impact of duration of adjuvant therapy (e.g., greater or less than 6 cycles of temozolomide chemotherapy). This study will not be powered to make meaningful inferences on the superiority of either intervention. However, to have a better estimate of event rate (death) over time in a larger phase III trial, we will perform time-to-event analyses to evaluate the primary outcome for the future trial of overall survival time. We will interpret the results of each outcome as follows.

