Clinicians must balance any potential survival benefits of the extent of surgical resection in HGG with the competing risk of potential surgical complications. While a more aggressive philosophy of surgical resection in well-selected patients can potentially improve survival, the potentially added risk of neurological deficit, which could in turn affect the quality of life (QOL) and eligibility for adjuvant therapy, must also be considered. We conducted an independent systematic review of the literature to search for studies investigating whether survival is improved with the extension of surgical resection beyond the enhancing margin of tumor and associated surgical risks. In order to achieve maximal sensitivity, we used a broad search strategy combining terms related to the condition (glioblastoma, high-grade glioma, malignant glioma) with terms describing the extent of surgical resection (marginal, beyond enhancing margin, supra-marginal, MR flair signal margin). Very few studies have examined these risks in detail [18, 19]. Two recent studies evaluated outcomes in a total of 51 patients with supra-marginal resection. One study was a parallel-group prospective study, and the other was a retrospective case series. Both studies revealed survival advantages compared to standard attempts at gross total resection with no additional perioperative surgical risk [20].

The evidence for supra-marginal resection thus far is low-quality and under-powered [18]. Therefore, there are no practice guidelines, and the philosophy of surgical resection is guided by individual surgeon preference on an individual patient basis. This creates additional uncertainty and is potentially detrimental to our patients. In preparation for this pilot study, we have also conducted a survey of Canadian neurosurgeons to evaluate the specialty’s perspective on supra-marginal resections. The most compelling result was that 90% of participants were willing to consider enrolling patients in a randomized controlled trial comparing supra-marginal vs conventional marginal resection (Additional file 6). Together, these findings demonstrate clinical equipoise, supporting the need for an adequately powered RCT to determine whether a supra-marginal resection can have a positive impact on survival for patients with HGGs.

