***Received > 90% of planned dose***			
***Early discontinuation < 50%***			
***Disease progression***			
***Toxicity***			
***Others***			

### Safety criteria

During this pilot study, several safety precautions are being implemented:i)A clearly defined definition of “surgically safe” anatomical criteria.ii)Confirming anatomical suitability by a second designated neurosurgeon centrally.iii)A central adjudication committee, comprising two qualified neurosurgeons, will confirm the suitability of all enrolled cases on an annual basis.iv)Establishing appropriate surgical expertise and volumes for participating surgeons (Additional file 2),v)Mandating minimum intraoperative use of 3D neuronavigation and neurophysiologic monitoring to guide resections for all patients.vi)Incorporating multiple interim safety analyses by the Data and Safety Monitoring Board (DSMB).

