### Procedures common to both groups

Imaging, concurrent non-experimental medications, and any adjuvant post-operative care, i.e., external beam radiation therapy plus concomitant and adjuvant temozolomide) including timing, will be according to the standard of care and be recorded. All surgeries will be performed by designated surgeons at each center meeting certain pre-defined surgical skill qualifications (Additional file 2). All surgeries will be performed with the help of intraoperative 3D neuronavigation tools and neurophysiologic monitoring defined by the continuous assessment of the functional integrity of the neural pathway. Other intraoperative adjuncts (e.g., fluorescence-guided, intraoperative MR) are allowed but not required (Additional file 3). The surgical technique (not the extent) for tumor removal is similar in both arms, minimizing any learning curve effect during the trial. Post-operative imaging follow-up with contrast-enhanced brain MRI will be conducted as per institutional practices at regular intervals.

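### Duration of temozolomide is listed as an a priori subgroup, but cycle count arises after randomisation and requires survival, so any survival comparison by cycles received, counted from randomisation, would be biased

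*Protocol article*

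**What the plan says.** The protocol article, Statistical methods, Secondary outcomes, states: "A priori subgroup descriptive comparisons will include our randomization strata", and adds to that list "the impact of duration of adjuvant therapy (e.g., greater or less than 6 cycles of temozolomide chemotherapy"). The same paragraph limits the claim: "This study will not be powered to make meaningful inferences on the superiority of either intervention". It then says "we will perform time-to-event analyses to evaluate the primary outcome for the future trial of overall survival time", to estimate the death rate for phase III. The subgroup sentence names neither the outcome to be compared nor the contrast (long versus short duration, or surgical arms within each duration group).

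On timing, Sequence generation says "Randomization will be done within 3 days prior to the scheduled surgery". Procedures common to both groups places "external beam radiation therapy plus concomitant and adjuvant temozolomide" in post-operative care. The Introduction says surgery may cause neurological deficit, "which could in turn affect the quality of life (QOL) and eligibility for adjuvant therapy". The temozolomide form printed after the Schedule of events has a row for "Disease progression" beside early discontinuation, toxicity and other reasons.

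**The concern.** A subgroup supports a fair comparison when membership is fixed before randomisation. The strata meet that condition; cycles received do not. Three things tie cycle count to what happens later:

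- A patient who dies early cannot reach the cut, so the long-duration group is selected for survival (immortal time).
- Progression appears on the temozolomide form, so membership is probably tied to a component of progression-free survival as well.
- By the Introduction's own account, surgery can change eligibility for adjuvant therapy, so the variable may lie between the randomised treatment and the outcome.

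At stake is a descriptive table or curve that appears to show a large benefit of longer chemotherapy, or a difference between surgical arms within a cycle group, that selection alone could produce. The word impact in the sentence invites that causal reading.

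**Working it through.** **Inputs from the protocol article.** Median overall survival 14 months and a meaningful hazard ratio of 0.7 (Adherence to protocol); 72 patients, 36 per group (Sample size). The subgroup sentence carries no figure. The plan's one survival calculation reproduces: deaths = 4(1.96 + 0.8416)² / (ln 0.7)² = 31.40 / 0.1272 = 246.8, or 247 as stated. This confirms 0.7 as a yardstick; the death count does not depend on the median.

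**Assumptions.** The article gives neither cycle length nor a completion rate. Let L be the months from randomisation needed to pass the cut (6 to 10) and q the share of patients alive at L who do so (30% to 90%). Survival is exponential and cycles have no effect.

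**Long versus short duration, survival from randomisation.**

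- Alive at L: S = 2^(−L/14), which is 0.743, 0.673, 0.640 and 0.610 at 6, 8, 9 and 10 months.
- Long-group median: L + 14.
- Short group: deaths before L plus non-completing survivors, a share 1 − qS of all patients. Its median m solves 2^(−m/14) = (1 + qS)/2 if m ≤ L, otherwise 2^(−m/14) = (1 − qS)/(2(1 − q)).
- Example, L = 9, q = 0.7: (1 + 0.448)/2 = 0.724, so m = 14 × log2(1/0.724) = 6.5.
- Example, L = 6, q = 0.3: 0.777/1.4 = 0.555, so m = 11.9.

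The hazard ratios below are medians from 3,000 simulated trials of 72 patients, with censoring uniform between 12 and 36 months.

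| L | q | Long median | Short median | HR, truth 1.0 |
|---|---|---|---|---|
| 6 | 0.3 | 20 | 11.9 | 0.57 |
| 6 | 0.9 | 20 | 3.7 | 0.19 |
| 8 | 0.5 | 22 | 8.3 | 0.41 |
| 9 | 0.7 | 23 | 6.5 | 0.27 |
| 10 | 0.3 | 24 | 10.9 | 0.40 |
| 10 | 0.9 | 24 | 5.2 | 0.12 |

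Over the full grid the hazard ratio runs from 0.12 to 0.57, always more extreme than 0.7. Were a 5% test applied, it would reject in 30% to over 99% of trials.

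**Same data with a landmark at L** (only patients alive at L, clock restarted). The hazard ratio is 0.87 to 1.01 at 72 patients and 0.98 to 1.03 at 20,000; rejection is 4.6% to 7.0%. The 0.87 is at L = 10, q = 0.9, where only about 72 × 0.610 × 0.1 = 4 non-completers remain.

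**Surgical arms within cycle groups** (L = 8, no true arm effect).

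- Completion 50% in both arms: HR 1.01 (long), 1.00 (short).
- Completion 50% versus 70%: HR 1.00 (long), 1.27 (short), against the arm that completes more often.
- Completion 50% versus 35%: HR 0.99 (long), 0.89 (short), in favour of the arm that completes less often.

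**The case against.** The article calls these comparisons descriptive and disclaims power for superiority. No test is attached to the split, and the 6-cycle cut is only an example. The survival analysis comes two sentences later and serves another purpose. The analysis plan, which is not shown, could specify a landmark. These points stand as limits on the claim. They do not remove it: a power disclaimer addresses imprecision, not systematic bias, and a median misleads without a p-value. The article itself places the grouping beside the strata, so this is a stated choice rather than an omitted detail.

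A reader might infer that the comparison will show a large effect even when none exists. The documents do not support that. The outcome and contrast are unstated, and arms compared within cycle groups show no false effect when survival and completion are equal. Quoting 23 versus 4.0 months alone would also overstate the size, because that figure puts every 9-month survivor in the long group.

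A reader might also infer that the result would steer phase III or hide surgical harm. Under Adherence to protocol, progression rests on recruitment and on unresolved concerns of the monitoring board, and the future sample size rests on the survival difference between interventions. Safety is read from NIHSS, mRS, EQ-5D and 30-day mortality, with six-monthly safety reports. None of these uses the cycle split.

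**Conclusion.** The concern holds in conditional form. Cycle count is a post-randomisation variable that depends on survival and plausibly on surgery and progression, so it does not belong among a priori subgroups beside the strata. If overall survival from randomisation is compared by cycles received, a true null would appear as medians of about 20 to 24 versus 4 to 12 months. That size rests on exponential survival with the protocol's 14-month median and on assumed timing and completion; the direction does not depend on where in those ranges the truth lies. If arms are compared within cycle groups, the comparison is not protected by randomisation and is biased when completion differs by arm, in either direction. The consequence is misleading descriptive survival results, not a wrong progression decision. As a smaller defect, the example cut leaves patients with exactly 6 cycles in neither group.

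**What to change.** - Remove duration of adjuvant therapy from the a priori subgroups and keep only factors known at randomisation.
- Report adjuvant therapy started, its timing and cycles received as outcomes by arm.
- If duration is to be related to survival, state the outcome and time origin, use a landmark or a time-dependent covariate, assign exactly 6 cycles to a group, and label the result non-randomised.

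The cost is about one sentence in the statistical methods. The Schedule of events already collects chemotherapy timing, and the temozolomide form records the share of planned dose and early discontinuation; a cycle count is needed for the planned split in any case. The downside is precision: a landmark drops patients who die before it, which under the 14-month median is about 72 × (1 − 0.743) = 19 patients at 6 months and 72 × (1 − 0.610) = 28 at 10 months.

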#### Adherence to protocol

We will define successful adherence as follows:i)Documenting every scheduled clinical assessment on day 2, day 30, 6 months, and 1 year (if alive) in at least 90% of patients.ii)*Implementation of the study protocol* by measuring in at least 90% of enrolled patients the planned primary outcome measure for the larger trial (i.e., overall survival). This rate is comparable to the ability to obtain an outcome in previous large glioma studies [9]

Any reasons for non-adherence to the protocol will be recorded to improve the future larger trial. We will also capture the amount of personnel time required to screen for, consent, enroll patients, complete study procedures, and data collection for the first 5 patients at each site. A strategy to refine the final protocol for the full-scale trial based on the results of the each of above steps will be planned.

The decision to progress to the larger phase III RCT will be based on (1) reaching the primary feasibility target of recruiting at least an average of 1 patient per 2 months per year in each of 6 centers during 2 years of active study participation at each center and (2) no safety or ethical concerns are raised by the Data and Safety Monitoring Board (DSMB) that cannot be rectified. For the future trial, we plan to use overall survival difference (i.e., hazard ratio) to determine the relative efficacy of the interventions and will use data from the pilot study to estimate the required sample size. A meta-analysis assessing 6-month PFS has favored GTR over subtotal resection (STR) (relative risk (RR) 0.72) [7]. For a supra-marginal resection to have a meaningful impact on the survival of HGG patients, a similar improvement of 0.7 hazard ratio would be desired. We calculated that a total of 295 patients (247 deaths) would be required for the trial to have 80% power to detect a hazard ratio of 0.7 (base median overall survival of 14 months) at a two-sided alpha 5% level and planned average length of follow-up of 2 years. Based on our plan to recruit 10 Canadian sites for the phase III study, with an average annual enrollment rate per site of 6 subjects with 2 active surgeons, we anticipate meeting the full enrollment target within 5.5 years. Assuming that there are no major changes to the pilot protocol, we will include the patients’ data in this future larger RCT.

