### Outcomes

#### Primary feasibility outcome

The primary feasibility outcome is the number of patients enrolled and successfully allocated to the study interventions per year during the duration of the pilot RCT at each study center. This number will determine whether a larger phase III RCT is warranted and feasible.

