### Sample size

The sample size is based on six sites enrolling patients in this pilot study. All six proposed pilot trial sites are academic tertiary care centers with at least 20–30 malignant glioma surgeries per year (assuming 5 per 100,000/year incidence of new HGG) out of which about one-third are eligible, and assuming that 70% will consent in the 2 years of active recruitment, we will be able to enroll between 45–105 patients. Based on our observational phase I trial (Additional file 4), we were able to enroll at least 1 patient per 2 months, and therefore, a sample size of 72 patients (36 per group) should be feasible for this pilot RCT. If at the end of the study period we recruit 72 patients, we will be 95% confident that these sites will be able to recruit over the same time interval between 56 and 91 patients.

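### The phase III progression rule, read as written, requires every one of six centres to reach the planned rate, which six on-target centres would do together about 2.4% of the time; the per-site monthly median may not show whether the rule was met

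*Protocol article*

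**What the plan says.** All references are to the protocol article.

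- **Adherence to protocol.** Progression needs at least an "average of 1 patient per 2 months per year in each of 6 centers during 2 years of active study participation". The sentence then attaches the two years to each centre again. The second condition is that the DSMB raises no safety or ethical concern that cannot be rectified. For phase III, the same section assumes an "average annual enrollment rate per site of 6 subjects with 2 active surgeons".
- **Objectives and Primary feasibility outcome.** The outcome is a yearly number of patients enrolled and allocated, defined centre by centre. Of it the article says: "This number will determine whether a larger phase III RCT is warranted and feasible".
- **Sample size.** Earlier experience is given as "we were able to enroll at least 1 patient per 2 months", from which "a sample size of 72 patients (36 per group) should be feasible for this pilot RCT". If 72 are recruited, "we will be 95% confident that these sites will be able to recruit over the same time interval between 56 and 91 patients".
- **Statistical methods, Primary outcome.** The analysis reports the "rate of randomization (patients per month) as overall and per site numbers using medians and interquartile ranges".

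The progression rule carries no margin or intermediate zone.

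**The concern.** One patient per two months for two years is 12 per centre, and six centres at 12 make exactly 72. The threshold therefore coincides with the planning rate. Attached to every centre separately, it has to be cleared six times over by counts that vary by chance, and one centre falling slightly short blocks progression. Attached to the six centres together, it is a very different rule. The article's wording favours the first reading, while its sample size section reasons about the sites together.

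This is the only numerical criterion for going to phase III, and it sits on the primary outcome. A workable programme could be declared infeasible by chance, or the decision could be disputed afterwards because two readings of one sentence give opposite answers. The planned descriptive summary adds to the difficulty: the rule is an average, but the per-site report is a median.

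**Working it through.** **Inputs.** Six centres, 24 months and 0.5 patients per month per centre (Adherence to protocol; Sample size). Phase III rate of 6 per site-year (Adherence to protocol). For the projection: "at least 20–30 malignant glioma surgeries per year" per centre, one third eligible, 70% consenting, two years (Sample size).

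**1. The plan's own figures.** 6 × 24 × 0.5 = 72. The exact Poisson 95% interval for a count of 72 runs from χ²(0.025; 144)/2 = 56.3 to χ²(0.975; 146)/2 = 90.7. This reproduces the stated 56 to 91, so Poisson counts are already the article's working model.

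**2. Rule read literally (every centre reaches 12).** With independent Poisson counts of mean 12:
- P(one centre has 12 or more) = 0.538
- P(all six) = 0.538^6 = 0.024

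If centres differ in their true rates (gamma, overall mean still 12, assumed shape 10 down to 2), this falls to 1.4% down to 0.6%.

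**3. Other true rates, both readings.** The projection inputs give 20 × 1/3 × 0.7 × 2 = 9.3 to 30 × 1/3 × 0.7 × 2 = 14 per centre. The section's stated upper total of 105 is 105/6 = 17.5 per centre.

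| True mean per centre | One centre ≥ 12 | All six ≥ 12 | Total ≥ 72 |
|---|---|---|---|
| 9.3 | 0.230 | 0.015% | 2.2% |
| 12 | 0.538 | 2.4% | 52% |
| 14 | 0.740 | 16% | 92% |
| 17.5 | 0.932 | 65% | over 99.9% |

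For an 80% chance that all six pass, the true mean must be about 18.9 per centre, or 18.9/12 = 1.57 times the planned rate.

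**4. The per-site median, if taken over monthly counts.** At 0.5 per month, P(no patient in a month) = exp(−0.5) = 0.607. The median is therefore 0 and the interquartile range 0 to 1. The median stays 0 while exp(−r) is at least 0.5, that is, up to r = ln 2 = 0.69 per month (0.69 × 24, about 16.6 patients in two years). The upper quartile is already 1 once exp(−r) drops below 0.75, at r = 0.29 (about 6.9 patients). Rates from 0.29 to 0.69 therefore share the same theoretical summary, 0 (0 to 1), on both sides of the 0.5 threshold.

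A centre with exactly 12 patients in 24 months has a median of 0 unless all 12 fall in different months. With patients spread at random that has probability 24!/(12! × 24^12) = 0.035, so the median is 0 in 96.5% of cases.

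**5. The overall monthly count.** At 6 × 0.5 = 3 per month the median is 3 (interquartile range 2 to 4), which is informative.

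**6. What phase III needs.** 295 patients at 10 sites in 5.5 years is 295/(10 × 5.5) = 5.4 per site-year. Over the pilot's 12 centre-years that is about 64 patients, if pilot patients are not counted towards phase III.

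**The case against.** The best defence is that the rule speaks of an average and the sample size section treats the sites as a group, so a pooled criterion of 72 may be what was intended. On that reading an on-target network passes about half the time. That is no defect in itself: any cut-off is met about half the time when the true rate sits on it. If 72 is the minimum acceptable count and the sponsor expects more, the rule works well (92% at a true total of 84). This stands, and it limits the pooled-reading concern to the missing statement of which role 72 plays. It does not remove the ambiguity, because both the rule and the primary outcome are worded centre by centre.

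Three stronger readings are tempting and are not supported:

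- A reader might infer that on-target centres almost never pass. That holds only for the literal reading.
- A reader might infer that all six centres need exactly 12, with probability 72!/(12!^6 × 6^72) = 0.005%. This assumes that enrolment closes at 72. The article sets no clear cap and describes a two-year window.
- A reader might infer that the primary analysis yields only zeros, or that the median decides progression. The zero arises only for within-site medians of monthly counts; the overall median is about 3, and a median of six site rates would be about 0.5. The decision uses an average, which the trial can compute from counts it holds anyway.

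It can also be said that operational detail may sit in the full protocol. The article does state the rule and the summary, however, and the point concerns what it states.

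**Conclusion.** The concern holds in this form. As worded, the rule requires each centre to reach the planning rate, and six centres truly at that rate would satisfy it about 2.4% of the time (0.015% to 16% over the 9.3 to 14 per centre that the article's own inputs imply). Pooled, the figure at the planned rate is about 52%, acceptable or not according to whether 72 is a floor or an expectation. Both figures assume Poisson counts, which match the article's own interval. The 2.4% also assumes independence between centres and equal true rates; the unequal rates tried above lower it.

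The median is a secondary, reporting fault. If per-site medians are taken over monthly counts, they cannot show whether the average-rate criterion was met, but they do not alter the decision.

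**What to change.** **Adherence to protocol.** Remove the requirement on each centre. State the criterion for the six centres combined: patients randomised divided by active centre-months, with site rates descriptive only. Say whether 0.5 per centre-month is the expected rate or the minimum acceptable one.

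**Statistical methods, Primary outcome.** Report that rate, overall and per site, with an exact Poisson 95% interval in place of medians of monthly counts. With 72 patients in 144 centre-months this would read 0.50 (56.3/144 = 0.39 to 90.7/144 = 0.63).

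**Cost.** No new data are needed. It does change a progression criterion in a protocol that the research ethics board has approved, so it should be handled as an amendment and made before recruitment results are known. The substantive downside is that one weak centre no longer blocks progression by itself; the descriptive site rates keep such a centre visible.

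Pooling alone leaves the pass probability at about 52% if 72 is the expected count. Whether to add a lower threshold or an amend zone is for the sponsor to choose; the documents do not fix one. Any choice should be consistent with the stated 5.5-year phase III accrual, which needs about 5.4 per site-year (about 64 over the pilot) if pilot patients are not counted, and less if they are.
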